# Contingency management for smoking cessation among individuals with type 2 diabetes: protocol for a multi-center randomized controlled feasibility trial

**DOI:** 10.1186/s40814-020-00629-7

**Published:** 2020-06-11

**Keywords:** Smoking cessation, Diabetes, Financial incentives, Contingency management, mhealth

## Abstract

**Background:**

Individuals with type 2 diabetes (T2D) who smoke are at increased risk for many types of cancers as well as an accelerated progression of microvascular and macrovascular complications. Smoking cessation is recommended as a standard treatment for T2D; however, individuals with T2D are faced with competing lifestyle changes. Glycemic and blood pressure control often take precedence over smoking cessation, and patients are often unmotivated to quit. Contingency management in combination with standard smoking cessation treatment has been demonstrated to improve cessation outcomes in various populations. The purpose of this randomized controlled feasibility trial is to explore the feasibility of contingency management and biochemical verification using a remote smartphone-based carbon monoxide monitor for smoking cessation among individuals with T2D.

**Methods:**

A three-arm, randomized controlled feasibility trial will be conducted in two study sites that include the USA and UK. We will recruit 60 participants who will each receive usual care smoking cessation treatment (counseling and nicotine replacement therapy) and be randomized to a short term incentives (6 weeks), long term incentives (12 weeks), or no incentives (control) group. Participants will receive a smartphone and carbon monoxide monitor to complete daily remote assessments throughout the 12 weeks and will complete an exit interview at the end of the study. The primary outcomes for this feasibility study include completion of the protocol and proportion of daily assessments completed. Secondary outcomes include recruitment measures, acceptability, and smoking abstinence.

**Discussion:**

We will explore the feasibility of recruiting smokers with T2D and their engagement in the program, particularly related to the use of the remote biochemical verification and smartphone application. In addition, we will evaluate the intervention content, study procedures, data collection methods, and follow-up and will qualitatively assess the participants’ acceptability of the program. The results of this study will inform the design of a larger trial to test the efficacy of the contingency management program for improving smoking cessation outcomes among individuals with T2D.

**Trial registration:**

This randomized controlled feasibility trial has been registered at ClinicalTrials.gov with an ID NCT03527667 on May 4, 2018.

## Background

Type 2 diabetes (T2D) and cigarette smoking are major causes of morbidity and mortality in the USA (US) and United Kingdom (UK) [1–5], and research indicates there is a complex relationship between these two risk factors [6–10]. Smoking is a major behavioral risk factor for many types of cancer, is associated with insulin resistance, and was listed as a causal factor for T2D in the 2014 Surgeon General’s Report [4, 6, 11]. The harms of smoking are particularly profound among individuals with T2D who continue to smoke, with an accelerated progression of microvascular and macrovascular complications and an increased mortality risk [7, 8, 12]. Individuals with T2D are also independently at increased risk for many cancers, although the link between T2D and cancer is currently not well understood [13, 14]. Evidence suggests biological mechanisms along with increased prevalence of behavioral risk factors play a key role [6, 14–16]. Despite the heightened risk for cardiovascular disease, cancer, and diabetes-related complications, many patients with T2D continue to smoke. As the prevalence of T2D in the US and UK population is expected to double in the next three decades, it is essential that we understand the impact of smoking on diabetes and health outcomes and identify ways to effectively integrate smoking cessation into diabetes care [5, 17].

As standard care, those diagnosed with diabetes who smoke are recommended by the American Diabetes Association and the UK’s National Institute of Health and Care Excellence to stop smoking; however, patients with T2D and their providers are often inundated with other challenging lifestyle changes and disease management strategies [18, 19]. Glycemic and blood pressure control through dietary changes often take precedence over cessation, and patients often feel unmotivated or are unable to quit smoking [19]. Due to the complex relationship between T2D and smoking and the large number of competing lifestyle changes recommended at diagnosis, smokers with T2D may benefit from a program that incentivizes smoking cessation.

Providing patients with tangible rewards to reinforce positive behaviors, such as smoking abstinence, has been proven effective during treatment in substance abuse programs, smoking cessation programs among pregnant women unwilling or unable to quit, and other population subgroups [1, 20–24]. Contingency management, or the exchange of a reward contingent upon verified smoking abstinence, in combination with standard smoking cessation treatment, has been demonstrated to improve cessation outcomes in various populations [1, 20, 24–29]. Few studies have examined the effects of a contingency management program or financial incentives for smoking cessation among individuals with chronic disease [30]. Through a retrospective analysis of randomized trials, Walter and Petry demonstrated that participants with diabetes responded well to contingency management as a treatment for substance abuse and that the effect of the incentives was greater than for individuals without diabetes [31]. Other studies among patients with diabetes have focused on contingency management for diabetes medication adherence [32, 33]. Despite the heightened risks of smoking-related outcomes among individuals with T2D, to our knowledge, contingency management has not been tested in this population as a smoking cessation intervention. It is unclear whether a contingency management program would be feasible and acceptable in this population.

The need to biochemically verify smoking abstinence daily creates a challenge for many contingency management programs for smoking cessation. Smoking abstinence is primarily verified through saliva, urine, or carbon monoxide (CO) assessments, but challenges around the costs, difficulty of administration, and logistics of daily testing has been a limiting factor in contingency management studies [26, 34]. Researchers have had to choose whether to place the burden of many in-person visits on the participants or incur significant data collection costs through daily home visits by study coordinators. With the rapid expansion and development of mobile health (mHealth) technology, there are now smartphone-based remote CO sensors that can be distributed to each research participant for daily verification of smoking abstinence [27, 34–36]. In addition, the combined use of a smartphone sensor and application (app) provides the opportunity for daily assessment of urges to smoke, motivation to quit, tobacco use, and medication adherence. If ultimately proven feasible and effective, this remote smartphone approach also provides a scalable and cost-effective means of delivering this intervention in a healthcare setting.

## Study aims and hypotheses

The research objectives and trial design were conceived and developed through a unique multidisciplinary and international collaboration formed during a knowledge integration sandpit event hosted by the US National Cancer Institute and Cancer Research UK. This was a residential workshop bringing together investigators from the UK and the US across different sectors and disciplines (e.g., academia, technology, epidemiology, psychology, community) to integrate knowledge about behavioral cancer risk factors, form new networks, and develop innovative research grant proposals in cancer prevention. Through this, we designed a randomized controlled feasibility trial to explore the acceptability and feasibility of a contingency management program for smoking cessation among smokers with T2D previously unable to quit. This pilot study aims to gather data in both the US and UK context related to the feasibility of conducting a contingency incentive-based program with remote biochemical verification using a smartphone-compatible CO monitor. This study explores two different lengths of contingency management (6 weeks vs 12 weeks) for this population using a smartphone app and remote CO sensor to monitor urges to smoke, stressors, smoking behaviors, and to validate abstinence daily throughout the intervention. The specific aims of the study are to:
Explore the feasibility of conducting a randomized controlled trial to compare the effect of two different contingency structures ($20 or £15 weekly incentives for 6 weeks vs 12 weeks) vs control (no incentives) on smoking abstinence.Explore the feasibility of remote CO testing using a smartphone-based CO sensor and mobile app to validate abstinence.Gather preliminary evidence and estimates of recruitment and eligibility rates, loss to follow-up, as well as the likely effect size of the intervention on smoking cessation to inform parameters of a large randomized controlled trial.Examine the acceptability of the intervention content, delivery mode, timing, adherence, and maintenance.Explore the potential unintended consequences (e.g., weight, glycemic control, perceived health) of the intervention.

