## Methods/design

### Study design

A three-arm, randomized controlled feasibility trial will be conducted in two study sites that include the US (Oklahoma City, Oklahoma, USA) and UK (Greater Glasgow, Scotland, UK). The US site is located at the University of Oklahoma Health Sciences Center (OUHSC) campus within the Tobacco Treatment Research Program that is a part of the Oklahoma Tobacco Research Center. This clinic provides in-person and telephone cessation services to the metropolitan area as well as surrounding towns. The UK site is located at the University of Strathclyde and Stop Smoking Services clinics located in Glasgow and Ayrshire and Arran.

This trial will include a baseline assessment (visit 1), quit date visit that occurs 1 week after the baseline assessment (visit 2), and a third follow-up visit (visit 3) at the end of the 12-week cessation program, or 13 weeks after the baseline visit. The participants will complete 12 total weeks of daily assessments using a smartphone beginning on the quit date (visit 2). The 12-week post-quit follow-up period coincides with the 12 weeks of nicotine replacement therapy (NRT) that participants are eligible to receive as part of their standard smoking cessation services.

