**Assessments**					
Biological/anthropometric measures	3	X	X		X
Demographic/background information questionnaire	10	X			
Tobacco history questionnaire	17	X			
Heaviness of smoking index	2	X			
Wisconsin smoking withdrawal scale—craving (past week)	4	X			
Self-efficacy scale/confidence	9	X			
Motivation to quit	3	X			
Diabetes questionnaire	5	X			
Diabetes self-management questionnaire	16	X			X
Consideration of future consequences scale	12	X			
Daily stress and anxiety	5			X	
Daily urges to smoke	4			X	
Daily mood and physical symptoms scale	12			X	
Daily self-efficacy/confidence/motivation	4			X	
Daily tobacco and medication use	7			X	
Daily diabetes and health questions	6			X	
Daily CO reading (iCO™ Smokerlyzer®)	1			X	
Study participation exit questionnaire	10				X

#### Assessments at visits 1, 2, and 3

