At all three in-person visits that will occur in the treatment clinics, biological/anthropometric measures will be collected by the research coordinator and entered into a secure REDCap database. These measures include height, weight, and tobacco use status measured through expired CO using a Vitalograph Breath CO monitor. At visits 1 and 3, additional measures will be obtained through self-administered surveys in REDCap using a tablet. Participants will complete 10 items related to demographics, which include sex, age, race/ethnicity, marital status, education, employment status, income, and the status of whether the participant lives with a smoker, has an active mobile phone, and if it is a smartphone. We developed a tobacco use history questionnaire that will capture 17 items related to current and past product, dose, and duration of use of tobacco, quit attempt history, perceptions of harm, comorbidities, and medication use. To assess dependence, participants will complete two items from the heaviness of smoking index [39] as well as 4 items from the Wisconsin smoking withdrawal scale for craving [40], both of which have been shown to be valid and reliable. We will use a 9-item self-efficacy scale/confidence to reflect the confidence that they can cope with high-risk situations without relapsing as well as 3 items assessing motivation to quit [41]. In addition to tobacco-related questions, participants will respond to diabetes-related questionnaires, which include a 5-item section related to age of diagnosis, diabetes control, and glycated hemoglobin and a 16-item diabetes self-management questionnaire assessing self-care activities related to diabetes [42]. Finally, we will collect measures of delayed gratification using the 12-item consideration of future consequences scale [43]. Table 1 outlines the assessments and number of items during the in-person visits.

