#### Daily assessments

Beginning at the quit date at week 1 throughout the duration of the 12-week intervention, we will use mobile-based daily assessments to validate abstinence and capture additional data related to stress and anxiety, urges to smoke, mood and physical symptoms, self-efficacy and confidence, motivation, tobacco and medication use, and diabetes information (Table 1). Daily assessments will be collected through the INSIGHT™ mobile health platform developed by OTRC [44]. We will purchase a Samsung Galaxy S7 phone in the US and a Samsung J3 Prime phone in the UK along with a 3-month data plan for each participant. Each participant will also receive a CoVita iCO™ Smokerlyzer® sensor to use throughout the study period. Using a smartphone application platform developed by the OUHSC OTRC mHealth Core, we programmed an app to collect our specific daily measures. The app will be installed onto the study phones and participants will be prompted through an evening alarm to submit daily CO readings (in ppm) and complete the daily assessment throughout the study period. The OUHSC mHealth Core has integrated the CO sensor into the platform with step-by-step instructions within the app that will collect assessment data so that participants will submit all measures in one cohesive assessment.

The daily assessment, estimated to take between 5 and 10 min, will begin with the CO reading followed by 5 items related to daily stress, which include the validated 4-item perceived stress scale [45]; 4 items assessing daily urges to smoke; the validated 12-item mood and physical symptoms scale [46]; 4 items related to self-efficacy, confidence, and motivation to quit; tobacco use, including products used, amount, and cessation medications; and 6 items related to diabetes management, which includes self-rated health, diabetes control, healthy food choices, and physical activity. Study coordinators will monitor compliance to daily assessments and will reach out to participants who quit completing assessments to encourage them to continue completing assessments.

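### Aim 5 covers glycemic control and perceived health, but the schedule gives glycated hemoglobin no follow-up value and self-rated health no value from before the quit date

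*Protocol article*

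**What the plan says.** Under Study aims and hypotheses, the fifth aim is to "Explore the potential unintended consequences (e.g., weight, glycemic control, perceived health) of the intervention". The measures that could serve it are spread over three places.

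- **Glycated hemoglobin.** The section on assessments at visits 1, 2, and 3 describes "a 5-item section related to age of diagnosis, diabetes control, and glycated hemoglobin". Table 1 lists this instrument as "Diabetes questionnaire 5 X", and the single mark stands in the visit 1 column. The separate 16-item self-management questionnaire is marked at visits 1 and 3.
- **Survey timing in the text.** The same section introduces the surveys with "At visits 1 and 3, additional measures will be obtained through self-administered surveys in REDCap using a tablet". It does not say which instruments are repeated.
- **Self-rated health.** The Daily assessments section lists "6 items related to diabetes management, which includes self-rated health, diabetes control, healthy food choices, and physical activity". Table 1 marks these items in the daily column only. Under Study design, daily assessments run for 12 weeks from the quit date (visit 2). Under Randomization, participants are told their arm at visit 2.
- **Weight.** It is measured at all three visits.

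**The concern.** The aim names three example consequences, and only weight is plainly measured both before and after the intervention. For glycated hemoglobin there is a starting value and nothing to compare it with. For self-rated health there are many later values but none from before the quit attempt or before the arm is known.

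These outcomes bear on possible harm in people with diabetes, and the study is meant to inform a larger trial. On this schedule the larger trial would receive no information on how glycated hemoglobin changes, or how variable that change is, in this population.

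The missing baseline for self-rated health has a second consequence. The health items are submitted in the same app session as the carbon monoxide reading, and incentives depend on those readings for 6 weeks, 12 weeks or not at all. The reason to keep submitting therefore differs by arm and over time, and the Discussion itself raises differential dropout among controls. Without a visit 1 value, nobody can check whether those who stop submitting already differed in self-rated health.

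**Working it through.** **Step 1: the plan's own number.** Participant eligibility and recruitment gives 10 per arm at each site: 2 sites × 3 arms × 10 = 60, which matches the stated total. Per arm this is 60 / 3 = 20. No alpha, power, SD or dropout figure is given for these outcomes, and the schedule finding needs none.

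**Step 2: measurement points, from Table 1 and the item descriptions.** Daily readings number at most 12 × 7 = 84 per participant.

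| Measure | Visit 1 | Daily from quit date | Visit 3 | What can be estimated |
|---|---|---|---|---|
| Weight | yes (also visit 2) | no | yes | change and arm difference |
| Glycated hemoglobin | yes | no | no | neither |
| Self-reported diabetes control | yes | up to 84 | no | arm difference; change if the two items have the same wording |
| Self-rated health | no | up to 84 | no | arm difference and post-quit trajectory; not change from before quitting |

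**Step 3: does the text override the table?** The sentence on surveys at visits 1 and 3 is true as soon as at least one survey is given at each visit, and the self-management questionnaire meets that. It does not place the 5-item questionnaire at visit 3. Table 1 sets timing instrument by instrument and treats the two diabetes questionnaires differently, so it is the more specific statement.

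**Step 4: what a baseline would add for self-rated health.** Take one post-quit summary per participant, 20 against 20, no dropout. In SD units,

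half-width = 1.96 × √[(2/20) × (1 − ρ²)],

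where ρ is the correlation between the visit 1 value and the post-quit summary. The documents do not give ρ, so it is assumed over a range:

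- no baseline (ρ = 0): 1.96 × √0.100 = 0.62 SD
- ρ = 0.3: 1.96 × √0.091 = 0.59 SD
- ρ = 0.5: 1.96 × √0.075 = 0.54 SD
- ρ = 0.7: 1.96 × √0.051 = 0.44 SD

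The arm contrast exists without a baseline. The baseline narrows it and supplies a pre-quit reference point.

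**The case against.** The case for leaving the plan alone has real weight.

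- **The aim is modest.** It is to explore, its outcomes are given as examples, and it does not define a consequence as change from baseline. Neither glycemic control nor perceived health appears among the outcomes under Feasibility outcome measures or in Table 2. This stands, and it limits how serious the point can be.
- **Perceived health is well observed after the quit date.** All three randomized arms give daily readings for 12 weeks, and Statistical methods plans mixed models for repeated data. This stands. A reader might infer that nothing can be learned about perceived health, or that the larger trial would get no estimate of its variability. The documents do not support that: arm differences, trajectories, and between- and within-person variability are all available.
- **Glycemic control is not only glycated hemoglobin.** Self-reported diabetes control is named both at visit 1 and in the app, so a baseline for a proxy may already exist. This stands in part. The wording of the items is not shown, and a self-rating is a weak substitute for a glycemic value.
- **Other sources feed the aim.** Self-care is measured at visits 1 and 3, and the exit interview asks about perceived impact on diabetes. This stands, but neither yields a glycemic value.
- **A self-reported value may be old.** Some participants will have had no new test since visit 1. This stands, so it would be wrong to count on 60 complete pairs after the fix. That figure is a ceiling before withdrawals and missing tests.

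**Conclusion.** The point holds in a limited form. For glycated hemoglobin it is complete: one scheduled value at visit 1, none afterwards, hence no change and no arm difference. For self-rated health the loss is confined to change from a pre-quit, pre-allocation value and to baseline adjustment. The precision at stake there is modest: a half-width of 0.62 SD becomes 0.59 to 0.44 SD for assumed correlations of 0.3 to 0.7, with 20 per arm and no dropout. Dropout would widen all of these figures.

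A reader might go further and say that two of the three named consequences cannot be answered. The schedule does not support that, because self-rated health and self-reported diabetes control are both followed daily in every arm.

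The conclusion rests on reading Table 1 as the governing schedule and on the article naming every place where glycated hemoglobin is asked. If the 5-item questionnaire was meant to be repeated at visit 3, then Table 1 is in error and should be corrected. In either case the table and the text on survey timing should be brought into agreement.

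**What to change.** - Repeat the glycated hemoglobin and diabetes-control items of the 5-item questionnaire at visit 3. At both visits, record the most recent glycated hemoglobin value and its test date.
- Ask the app's self-rated health item once at visit 1. Do the same for the app's diabetes-control item if its wording differs from the visit 1 version.
- Mark these in Table 1, and state in the text on the three visits which surveys are repeated.
- Estimate arm differences adjusted for the visit 1 value and site, labeled exploratory. Report how many glycated hemoglobin values at visit 3 come from a test after the quit date.

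The cost is a few more items on the tablet survey already in use, with no added visit or laboratory test. Some glycated hemoglobin values will still be missing or predate the quit date. The test date will show which, and such values should not be read as evidence of no change.
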